##### Patient-reported health outcomes

Patients’ actual choice regarding breast reconstruction will be measured by patient-report at postsurgical follow-up (T2, T3), and will be verified against patients’ EMR. Patient satisfaction with the breast [49], body image [58], sexual functioning [58], and breast symptoms [58] will be obtained at postsurgical follow-up. Anxiety will be measured at all four time points [59].

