### Randomization

Simple randomization stratified by site and patients’ surgical treatment options (e.g., whether the patient is eligible for both mastectomy and BCS or for mastectomy only) will be used to assign participants to the intervention group or the control group. Randomization ratio is 1:1. Randomization will be performed with ALEA software. This study is non-blinded, since blinding was not considered feasible due to the nature of the trial.

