### Statistical analyses

Data will be pseudonymized prior to data analysis and will not be traceable to any individuals. Depending on the level of measurement, analysis of variance or appropriate non-parametric statistics will be used to evaluate the comparability of baseline sociodemographic and clinical characteristics between the intervention and the control group. If differences in background characteristics are found, these will be taken into account in the subsequent analyses. Scores on the questionnaires will be calculated according to published scoring algorithms.

We will look at group differences in decisional conflict for the entire study duration (T0 to T3) using a mixed effect growth model with random intercept and slope and site as a cluster variable. This approach takes into account the within and between person variability, and deals adequately with missing data [66]. A comparable mixed effect model approach will also be used to determine the effects of the pDA on other patient reported outcomes. Differences in mean change scores over time between the intervention and control group will be accompanied by effect sizes (ES). An ES of 0.2 is considered small, 0.5 moderate and 0.8 large [67].

Analyses will be done on an intention-to-treat basis. As a secondary analysis, per-protocol analyses will be carried out on data from patients who meet the criteria for minimal compliance (to be determined). Appropriate statistical measures will be taken to adjust for multiple comparisons.

To evaluate between-group differences over time in categorical variables such as the actual choice in breast reconstruction, generalized estimating equations for longitudinal data will be used. This approach accounts for correlated within subject responses, allows for not normally distributed variables and deals adequately with missing data [68, 69].

We will explore which variables are predictive for the efficacy of the pDA on the primary outcome (decisional conflict) within the intervention group. A mixed effect model for longitudinal data will be used with decisional conflict as dependent variable and the following independent (baseline) variables: knowledge of breast reconstruction, patients’ preferred level of involvement in decision making, information coping style, and sociodemographic variables. The *p*-values for each model will be adjusted for multiple comparisons.

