### Power calculation

Power calculations for estimating sample size requirements were based on the following criteria: (1) power of 0.80, (2) alpha of 0.05, and (3) an ES d of 0.4. With these criteria a total sample size of 198 cases (99 per group) is needed. To allow for an anticipated attrition rate of approximately 20%, we will recruit 250 participants.

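### The article credits GEE with the same handling of missing data as the mixed model, but unweighted GEE generally needs data missing completely at random; the exposure is confined to secondary, questionnaire-only categorical items

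*Protocol article*

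**What the plan says.** All statements below are from the Protocol article.

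- **Categorical outcomes (Statistical analyses).** For between-group differences over time in categorical variables, with actual choice of reconstruction as the example, "generalized estimating equations for longitudinal data will be used". The reason given is "This approach accounts for correlated within subject responses, allows for not normally distributed variables and deals adequately with missing data [68, 69".
- **Continuous outcomes (Statistical analyses).** For the mixed-effect growth model on decisional conflict, which is extended to other patient-reported outcomes: "This approach takes into account the within and between person variability, and deals adequately with missing data [66".
- **Attrition (Power calculation).** "To allow for an anticipated attrition rate of approximately 20%, we will recruit 250 participants". No rate is given by arm or by outcome.
- **Source of the named GEE outcome (Patient-reported health outcomes).** On where this information comes from, the section states: "Patients’ actual choice regarding breast reconstruction will be measured by patient-report at postsurgical follow-up (T2, T3), and will be verified against patients’ EMR". Table 2 likewise lists both patient report and EMR data for this outcome.
- **Other categorical items (Table 2).** Satisfaction with information includes two yes/no questions, marked at T2 and T3 and answered by questionnaire only. The one-item Control Preferences Scale is marked at T1 and T2 as an outcome.

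**The concern.** Both methods are presented as coping with missing data, with no condition attached to either. For the mixed model the statement is defensible: with a correctly specified likelihood, dropout may depend on anything observed and included in the model. Unweighted GEE has no likelihood. Its estimating equations are averaged over whoever responded, so they have mean zero in general only under MCAR, or when missingness depends only on model covariates such as arm, site or visit.

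This is a positive statement that is wrong in general, not a detail left to an analysis plan. It tells whoever writes that plan that nothing further is needed.

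In this trial the MCAR condition could fail. Allocation is unblinded and follow-up runs to 12 months after surgery. The Discussion itself cites an earlier study in which 27% of enrolled women left on being randomised to a control group without additional information. Dropout that differs by arm alone would not bias GEE with arm in the model. But if reasons for leaving differ by arm and are related to earlier answers, an arm difference in a yes/no item can be created or diluted by dropout. That result would also rest on a stronger assumption than the continuous outcomes beside it.

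**Working it through.** **1. The plan's own figures.** With d = 0.4, two-sided alpha 0.05 and power 0.80, n per arm = 2 × (1.96 + 0.8416)² / 0.4² = 98.1, so 99 per arm. This matches "a total sample size of 198 cases (99 per group) is needed". Inflating for attrition, 198 / (1 − 0.20) = 247.5, so 248, against 250 recruited. The sample size is sound; the point concerns bias, not N.

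**2. Set-up (assumed; the article gives none of these figures).** A binary item is measured at T2 and T3. Let p be the proportion answering yes at T2. The chance of yes at T3 is 0.7 after a yes and 0.1 after a no. Let d1 and d0 be the dropout between T2 and T3 after a yes and after a no. With an independence working correlation and a mean model saturated in arm and visit, GEE converges to the proportion among those observed:

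T3 limit = [p(1 − d1) × 0.7 + (1 − p)(1 − d0) × 0.1] / [p(1 − d1) + (1 − p)(1 − d0)]

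**3. Mechanism differs by arm, true difference 0.** Take p = 0.3 in both arms, so the true T3 rate is 0.3 × 0.7 + 0.7 × 0.1 = 0.280.

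- pDA arm, dropout 20% regardless of answer: limit 0.280.
- Control arm, d1 = 0.45 and d0 = 0.10 (overall 0.3 × 0.45 + 0.7 × 0.10 = 20.5%): (0.165 × 0.7 + 0.63 × 0.1) / (0.165 + 0.63) = 0.1785 / 0.795 = 0.2245.
- Spurious difference: 28.0% − 22.5% = 5.5 points.

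**4. Same scenario, exchangeable working correlation.** GEE now adjusts the T3 mean for the imbalance that dropout produced at T2:

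μ(T3) = m(T3) − ρ × √(v(T3)/v(T2)) × [m(T2) − μ(T2)]

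Here m is the mean among completers, v = μ(1 − μ), and ρ is estimated from the observed pairs. In the control arm the completers' T2 rate is 0.165 / 0.795 = 0.2075, against 0.30 among all women. Solving to convergence in the large-sample limit:

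| Estimation of ρ | Control T3 | pDA T3 | Spurious difference |
|---|---|---|---|
| One ρ for both arms (about 0.56) | 27.5% | 28.0% | 0.5 points |
| ρ estimated within each arm | 27.0% | 28.0% | 1.0 point |

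**5. Same mechanism in both arms, true difference 6.0 points.** Take p = 0.3 v 0.2, so true T3 rates are 28% v 22%, with d1 = 0.40 and d0 = 0.12 in both arms (overall dropout 20.4% and 17.6%). Independence gives 23.6% v 18.7%, a difference of 4.8 points. An exchangeable correlation gives 5.6 points (common ρ) to 6.0 (ρ by arm).

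**6. A second set of assumptions.** The true rate is 50% in both arms, within-person correlation is 0.3 to 0.6, overall dropout is 20%, and the working correlation is independence.

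| Dropout mechanism | Bias in risk difference (size) |
|---|---|
| MCAR | 0 |
| Related to earlier answer, same in both arms | 0 |
| Same in both arms, but true rates 50% v 65% | 0.2 to 0.5 points |
| Related in one arm only (30% v 10% by earlier answer) | 1.9 to 3.8 points |
| Opposite directions by arm (30/10 v 10/30) | 3.8 to 7.5 points |

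Worked example for the one-arm row at correlation 0.3: the chance of yes is 0.65 after a yes and 0.35 after a no. With 10% dropout after yes and 30% after no, the limit is (0.45 × 0.65 + 0.35 × 0.35) / 0.80 = 0.519 against 0.500. With an exchangeable correlation all these biases are about 0.

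**7. What the working correlation cannot repair.** It uses only an earlier answer to the same item. The information items start at T2, so a woman lost before T2 contributes nothing under any working correlation. Nor is dropout that depends on another measure, such as T1 decisional conflict, corrected in this way.

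**The case against.** Much can be said on the other side.

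- **The named outcome has another source.** Actual choice is checked against the EMR, so questionnaire attrition is not its missingness rate. This stands.
- **The other GEE outcomes are inferred.** The article does not name the yes/no items or the Control Preferences Scale as GEE outcomes. The Scale is a 5-point item that could fall under the mixed model, and as an outcome it is marked only at T1 and T2. This also stands, and leaves the yes/no information items as the main exposure.
- **The larger bias needs an independence working correlation, which the article does not state.** Choosing GEE partly because it allows for within-subject correlation sits better with a non-independence structure. This stands, and it cuts 5.5 points to between 0.5 and 1.
- **The arm-specific dropout pattern is assumed.** The leaflet was given to controls partly to limit their dropout, and up to three reminders and a paper option are provided. This stands. Obligatory items, however, prevent skipped questions, not dropout.
- **Weighting, imputation and working correlation belong in a full protocol or analysis plan.** Agreed: their absence is not the point. What remains is the unqualified statement itself, which is incorrect in general for the unweighted method.

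A reader might infer that the trial's main result, or its result on reconstruction choice, is at risk. The documents do not support that: decisional conflict is analysed by a mixed model, and choice has EMR data. A reader might also infer that GEE must be abandoned. That is not needed, since a logistic mixed model estimates a subject-specific effect and would have to be marginalised for reporting.

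**Conclusion.** The point holds in a limited form. The article gives unweighted GEE a property that it generally lacks and that the mixed model, described in the same terms, does have. The consequence falls on secondary, questionnaire-only categorical items, chiefly the two yes/no information questions at T2 and T3.

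The size is conditional. With about 20% dropout and a mechanism that differs by arm, the illustrated null shows about 5.5 points under independence and 0.5 to 1 point under an estimated exchangeable correlation. With a common mechanism, bias is nil at the null, and under an exchangeable correlation it is small otherwise. The response rates, the link between visits and the dropout patterns are all assumptions. The article supplies only the 20% overall figure, so 5.5 points is an illustration of what the statement overlooks and not a forecast.

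**What to change.** - Keep GEE as the marginal model, but precede it with multiple imputation carried out separately by arm, using T0 data and earlier responses. Inverse-probability weighting is an alternative. Categorical outcomes then rest on the same MAR assumption as the continuous ones, and women lost before the first categorical response are covered too.
- Specify a non-independence working correlation.
- Take actual reconstruction choice from the EMR for every randomised woman, whether or not she returns the questionnaire.
- Replace the unqualified sentence about GEE with the missing-data assumption actually relied on.

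The cost is a change of wording and modest extra programming. The sample size stays at 198 evaluable and 250 recruited, and the primary analysis is untouched.

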Worldwide, only a limited number of interventions to support patient decision making about breast reconstruction are available [34]. In a recent review assessing the effectiveness of these interventions as compared to a control group, eight studies on seven distinct interventions were identified [34]. While the intervention improved patient satisfaction and involvement in decision making in all studies that reported on that specific outcome, results on other important outcomes were mixed [34]. In three out of five studies the intervention reduced decisional conflict [35–37], in two out of three studies the intervention reduced regret [35, 38] and in one out of three studies the intervention improved knowledge [39]. Furthermore, most included studies were rated as of weak methodological quality and none were undertaken in a European country.

To support women in making an informed decision regarding immediate breast reconstruction following mastectomy, we developed an online pDA for the Dutch population. The aim of this study is threefold. First, we aim to investigate the impact of this pDA on the decision-making process (in terms of decisional conflict, satisfaction with information, satisfaction with plastic surgeon, preparedness for decision making, perceived shared decision making, and involvement in decision making), on decision quality (in terms of knowledge of breast reconstruction and decision regret), and on patient-reported health outcomes (in terms of actual choice, satisfaction with breast, body image, sexual functioning, anxiety, and breast symptoms). Second, we aim to explore factors that are predictive of the effectiveness of the pDA. And third, the cost-effectiveness will be investigated.

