### Eligibility criteria

The study sample will be composed of women (≥18 years of age or older) diagnosed with breast cancer or ductal carcinoma in situ, who will undergo mastectomy, are eligible for immediate breast reconstruction and have been referred to a plastic surgeon. The consultation with a plastic surgeon should be scheduled at least three working days after study invitation, to allow participants for sufficient time to complete informed consent (IC) and the baseline questionnaire and use the pDA or information leaflet prior to their consultation. Additionally, women must have internet access, basic computer skills and sufficient command of the Dutch language.

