### Moderating measures

At baseline, we will measure patients’ preferred level of involvement in decision making regarding breast reconstruction (Control Preferences Scale [54]), preference for breast reconstruction (1 item, 5 point Likert-type Scale, with 1 = “I have a strong preference for undergoing breast reconstruction”, and 5 =“I have a strong preference for not undergoing breast reconstruction”) and information coping style (Threatening Medical Situations Inventory [63]). At all assessments, patients will be asked to report on the information sources they used regarding breast reconstruction.

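### Baseline preference for reconstruction is declared a moderator but is missing from the predictor model, and that model, fitted in one arm, could not test it as a moderator

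*Protocol article*

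**What the plan says.** The Background of the protocol article sets the second aim: "Second, we aim to explore factors that are predictive of the effectiveness of the pDA".

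Under the heading "Moderating measures", the article lists three scales taken at baseline: preferred involvement in the decision (Control Preferences Scale), "preference for breast reconstruction (1 item, 5 point Likert-type Scale"), and information coping style (Threatening Medical Situations Inventory). Score 1 on the preference item is a strong wish for reconstruction and score 5 a strong wish against it. The same section adds information sources used, asked at every assessment.

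Under Statistical analyses, the model for the second aim is to find variables "predictive for the efficacy of the pDA on the primary outcome (decisional conflict) within the intervention group". It is a longitudinal mixed model with decisional conflict as the dependent variable. Its independent baseline variables are enumerated as "knowledge of breast reconstruction, patients’ preferred level of involvement in decision making, information coping style, and sociodemographic variables", with p-values adjusted for multiplicity.

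Under Eligibility criteria, women must be such that they "are eligible for immediate breast reconstruction and have been referred to a plastic surgeon". No criterion concerns how settled their choice is.

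**The concern.** The list in the analysis section is stated as the set of variables to be used. It is not introduced as a set of examples, and it is not deferred to a later document. It takes up two of the three baseline moderators and leaves out the third, so two sections of one article disagree about what the second aim will examine.

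Preference for reconstruction is a natural candidate moderator. The primary outcome is defined as uncertainty about which course to take, and the Considerations module of the decision aid asks women to weigh immediate reconstruction against none and to state a preference. How settled a woman already is could plausibly change what that module does for her.

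If the item is brought in only after outcome data have been seen, any finding on it will be post hoc. If it is never brought in, a declared and collected measure goes unused. The article foresees nationwide implementation after a positive result, so who benefits is a practical question.

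**Working it through.** **Step 1: the two lists side by side.**

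| Baseline variable | Moderating measures | Predictor list, Statistical analyses |
|---|---|---|
| Preferred involvement | yes | yes |
| Preference for reconstruction | yes | **no** |
| Information coping style | yes | yes |
| Knowledge of reconstruction | no (an outcome, also taken at T0) | yes |
| Sociodemographic variables | no | yes |

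A stated preference for or against an operation is not a sociodemographic variable, so the last row does not cover it. The check of baseline comparability concerns sociodemographic and clinical characteristics and serves adjustment for imbalance, not moderation. The cost-effectiveness section does not use the item. Information sources are also absent from the list, but they are asked repeatedly, mostly after randomisation, so their absence from a list of baseline variables is less surprising.

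**Step 2: what the model can show.** Within the intervention group every woman has the decision aid. A coefficient for baseline variable X is then the association of X with conflict given the aid. It mixes the prognostic effect of X with any modification of the aid's effect, and only a comparison with the leaflet arm separates them. In a both-arm model with treatment T,

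E(DCS) = b0 + b1·T + b2·X + b3·T·X,

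the slope of X in the intervention arm is b2 + b3, and moderation is b3 alone. The planned fit returns the sum. This holds for every variable on the list, not only for preference.

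**Step 3: the plan's own sample size.** Inputs from Power calculation: power 0.80, alpha 0.05, d = 0.4. Sidedness is not stated; two-sided is assumed.

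n per arm = 2(1.96 + 0.84)² / 0.4² ≈ 98.1, so 99, or 198 in total. This agrees with the statement that "a total sample size of 198 cases (99 per group) is needed". One-sided testing would give 78 per arm and does not fit. With 20% attrition, 198 / 0.8 = 247.5, so 248, against 250 planned. The figures reproduce.

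**Step 4: what that sample gives for the interaction.** Assumptions: 99 evaluable per arm, SD = 1, preference split into two groups with share p in one of them, two-sided 5%, and no multiplicity adjustment. The article gives no distribution of preference, so p is varied.

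SE of the difference in effects = √[(2/99)(1/p + 1/(1−p))]

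Detectable difference at 80% power = 2.80 × SE; power for 0.4 SD = Φ(0.4/SE − 1.96)

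| Split | SE | Detectable difference (SD) | Power for 0.4 SD |
|---|---|---|---|
| 50/50 | 0.284 | 0.80 | 29% |
| 30/70 | 0.310 | 0.87 | 25% |
| 20/80 | 0.355 | 1.00 | 20% |
| 10/90 | 0.474 | 1.33 | 13% |

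With preference kept as a linear standardised score, SE = √(4/198) = 0.142, and the detectable interaction is about 0.40 SD per SD of preference. Multiplicity adjustment would lower these powers.

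**The case against.** The strongest case against is that this is a small mismatch in an exploratory analysis, that the item will be collected anyway, and that coding and ordering of moderators are commonly left to an analysis plan. The first two parts are right and set the severity. The third does not remove the point: the article states a list, and that list disagrees with its own measures section.

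A reader might infer more than this, and the documents do not support it:

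- **That preference is the factor most likely to decide who benefits, because only referred women enter.** The article gives no distribution of preference and ranks no moderators. Referred women are the intended users of an aid built to prepare them for the plastic surgeon. If referral did narrow the range of preference, the item would be harder to detect as a moderator.
- **That it is the only measure of how undecided women were.** The DCS is taken at T0 with its uncertainty subscale; only the effective decision-making items are left out. T0 conflict also enters the primary growth model. So the trial will have data to distinguish an ineffective aid from a sample that had already decided. What it lacks is a planned analysis of the preference item.
- **That a strong preference leaves little conflict to reduce.** The DCS also covers feeling informed, clear about values and supported, and the aid also addresses timing and type of reconstruction. A woman who firmly wants reconstruction may still be in conflict about these.
- **That the overall effect is diluted to a known degree.** One can compute 0.4 × (1 − 0.30) = 0.28, 0.4 × 0.50 = 0.20 and 0.4 × (1 − 0.70) = 0.12. But the shares of 30, 50 and 70% and the zero effect in women with a strong preference are invented, and in the article 0.4 is the effect for the whole sample.

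It is also fair to object that the interaction will probably be inconclusive. The table in the working bears this out. It is a reason to report an estimate with its interval and not to rest a conclusion on a p-value.

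**Conclusion.** The point holds as a minor inconsistency. Preference for reconstruction is a declared and collected moderator, is absent from the stated predictor list, and has no other analysis in the article. This rests on the text alone and needs no assumption.

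It carries a second element: any variable on that list, preference included, is tested in a form that cannot show moderation, because the model uses one arm.

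The primary comparison, its error rate and the sample size are untouched. The interaction that would answer the question has about 25 to 29% power for 0.4 SD at assumed splits of 30/70 to 50/50, and less with a more uneven split. The documents do not justify ranking preference above the other moderators.

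**What to change.** Reconcile the two sections:

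1. Add baseline preference for reconstruction to the independent variables under Statistical analyses, both as direction (the score from 1 to 5) and as strength (distance from the midpoint: 0 for score 3, 1 for 2 or 4, 2 for 1 or 5). The article labels only the end points, so taking 3 as undecided should be stated.
2. Estimate it in both arms as a treatment-by-preference interaction on the DCS, and report the difference between decision aid and leaflet by strength of preference. The other listed moderators need the same both-arm form if the aim is to learn who benefits. If the model within the intervention group is kept, describe it as showing who has lower conflict with the aid.
3. Label the results exploratory and give confidence intervals.

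The cost is small. The item is already asked at T0 and the sample size does not change. The price is a further term in the multiplicity adjustment, a model extended to the control arm, and an interaction estimate that will be imprecise. The change should be fixed before outcome data are compared by arm.
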